
Establishing a diagnosis for CI requires a comprehensive approach and an overall assessment of the patient’s cognitive performance using multiple diagnostic tools and is strictly the physician’s responsibility (21). Brief screening tests such as the Mini-Mental State Examination (MMSE) (22), the Clock Drawing Test (CDT) (23), and the Montreal Cognitive Assessment (MoCA) are used for an indicative examination of cognitive abilities. The MoCA test is a gold standard, one of the most commonly used cognitive screening tools worldwide. It is characterized by a high sensitivity and specificity for MCI (21), and short and standard versions of the MoCA appear to be effective in identifying CI (24). It was translated into many languages, including Slovak (25, 26). Its time-saving short version for pharmacy practice is suitable (27–29). If poorer cognitive abilities are noted in an orientation cognitive screening within pharmaceutical care, it does not mean the patient suffers from CI. A suspected CI is suggested. A physician’s assessment of the patient’s cognitive status is needed to confirm the CI (21).

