**Figure 3 fig3:**
[figure not shown]
Analysis plan – counseling between pharmacist and patient.

According to results of screening and pharmacist’s consideration, patients may be referred to a physician if their condition requires it. In such cases, the pharmacist will use the uniform information form for the physician (Supplementary Table 3). The patient receives an examination report informing the physician of the findings.

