**Figure 4 fig4:**
[figure not shown]
Analysis plan – counseling between pharmacist and physician.

The result of the pharmacotherapy analysis will be received only by a doctor. The patient will not be given the results to maintain adherence. Every patient in the study should be referred to a general practitioner for a preventive check-up if they have not had one in the last 2 years. During follow-up, the pharmacist will contact patients electronically to obtain feedback on whether they have addressed their condition with a doctor and whether the presence of CI has been confirmed.

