## Outcomes

3

In this study, we focus on a cohort of adults aged 50+ with lower cognitive abilities expressed by s-MoCA scores (≤ 12 points). These patients will be defined as those with suspected CI (CI+) who will be referred for medical examination. We will then record whether a physician has confirmed our suspicion of CI.

In the CI+ group, we will collect data on the prevalence of CI risk factors (expressed by CAIDE score) and the use of risk medications (expressed by ACB score) and then compare them with a control group.

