#### Hypotheses

5.1.2

According to our previous results, we hypothesize:

Short cognitive screening, a part of advanced pharmaceutical care, can help identify patients who need further cognitive evaluation by a general practitioner or a specialist.Analysis of pharmacotherapy can help to identify at-risk medication use related to CI.

Pharmacists in a community pharmacy could help monitor modifiable risk factors of CI.

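### Physician confirmation of CI is made with the s-MoCA result in hand, reported back by the patient and not tied to a new assessment, so the confirmed share is not an unbiased measure of how often a positive screen is right

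*Protocol article*

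**What the plan says.** Section 3 (Outcomes) defines the CI+ group by an s-MoCA score of 12 or less and continues: "These patients will be defined as those with suspected CI (CI+) who will be referred for medical examination". The next sentence gives the outcome: "We will then record whether a physician has confirmed our suspicion of CI".

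Section 2.9 (Patient counseling) has the pharmacist complete a standard form for the physician (Supplementary Table 3, not shown) and adds: "The patient receives an examination report informing the physician of the findings".

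Section 2.10 (Physician referral) states how the answer is obtained: "During follow-up, the pharmacist will contact patients electronically to obtain feedback on whether they have addressed their condition with a doctor". The same sentence adds a second question, whether CI was confirmed. Neither item asks what the doctor did.

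Section 1.1 says that diagnosing CI "requires a comprehensive approach and an overall assessment" with more than one diagnostic tool, that poor performance on a screen does not establish CI, and that a physician has to assess the patient to confirm it. Section 5.1.2 (Hypotheses) says that screening can help find patients who need "further cognitive evaluation by a general practitioner or a specialist".

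**The concern.** Confirmation is the only outcome in the article that sets a positive pharmacy screen against anything outside the pharmacy. Three stated features weaken it.

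- The physician knows the s-MoCA findings, so the judgement is not independent of the test being checked.
- The datum is the patient's account of what the doctor concluded, and these are patients in whom impairment is suspected.
- The two follow-up questions record a specialist work-up and a practitioner's agreement with the report in the same way. In the second case the screen would serve as its own reference (incorporation bias).

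The article does not call the confirmed share a positive predictive value, but readers are likely to take it as evidence that positive screens are right. If what the doctor did is not asked at follow-up, it will be hard to recover later. Section 4 lists measures against selection, observer and social desirability bias; none concerns the confirming physician's knowledge of the screen.

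**Working it through.** **The plan's own figure.** The article gives no number for the confirmed share. Its one computed design figure, 385, is for a single proportion and does not bear on this point. It reproduces if a proportion of 0.5 is assumed: n0 = z² × 0.25 / 0.05² = 384.15; with N = 2,033,555, n0 / (1 + (n0 − 1)/N) = 384.07, rounded up to 385.

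**Inputs.** The documents give no share with CI among CI+ patients, no physician accuracy, no acceptance rate and no response rate. Every value below is an assumption chosen to show a range.

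**Step 1: acceptance without a new test.** Suppose 40% of CI+ patients have CI on independent assessment, a fraction s is accepted without testing and recorded as confirmed, acceptance is unrelated to true status, and the remaining assessments are correct. Then the confirmed share = (1 − s) × 0.40 + s.

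| s | Confirmed, as worded | After further assessment, (1 − s) × 0.40 | Accepted only, s |
|---|---|---|---|
| 0.10 | 46% | 36% | 10% |
| 0.30 | 58% | 28% | 30% |
| 0.50 | 70% | 20% | 50% |

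This formula can only move upward, so it illustrates one mechanism and says nothing about the net bias.

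**Step 2: allow the physician to err in both directions.** Let p be the true share with CI among CI+ patients, and Se and Sp the physician's sensitivity and specificity. Confirmed share = p × Se + (1 − p) × (1 − Sp). For example, with p = 0.50, Se = 0.90 and Sp = 0.75: 0.45 + 0.125 = 57.5%.

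| Physician (Se/Sp) | p = 30% | p = 50% | p = 70% |
|---|---|---|---|
| A. Independent (0.80/0.90) | 31.0% | 45.0% | 59.0% |
| A. Influenced by the report (0.90/0.75) | 44.5% | 57.5% | 70.5% |
| A. Strongly influenced (0.95/0.60) | 56.5% | 67.5% | 78.5% |
| B. Independent, low detection (0.50/0.95) | 18.5% | 27.5% | 36.5% |
| B. Low detection, influenced (0.60/0.85) | 28.5% | 37.5% | 46.5% |

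Relative to the independent physician of the same type, influence adds 11.5 to 13.5 points (A), 19.5 to 25.5 points (A, strong) and 10 points (B). Every one of these differences is upward.

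Relative to the true share p, the influenced rows give +14.5, +7.5 and +0.5; +26.5, +17.5 and +8.5; and −1.5, −12.5 and −23.5 points. The sign is not fixed.

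**Step 3: non-attendance and non-response.** If patients without an answer stay in the denominator, the share is multiplied by the response rate r. With Se/Sp of 0.90/0.75, it falls below p once r drops below p divided by the confirmed share: 0.30/0.445 = 67%, 0.50/0.575 = 87% and 0.70/0.705 = 99%.

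**The case against.** A reader might infer that any physician's statement counts as confirmation and that the confirmed share is therefore inflated as a measure of how well the screen works. The documents do not support this.

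- No passage says that mere acceptance of the screen is counted. Section 1.1 describes confirmation as a physician's assessment, and Section 3 sends CI+ patients for medical examination. The mention in Section 5.1.2 of a general practitioner or a specialist concerns who may evaluate a patient; it is not a counting rule.
- The direction cannot be derived. Under-diagnosis, non-attendance and non-response pull the share down.
- The objectives and Section 4 contain no accuracy aim or analysis. Only CI+ patients have a planned confirmation outcome, so the share could at most speak to predictive value, never to sensitivity or specificity.
- This is a condensed article. Figure 4 and Supplementary Table 3 are not shown, and detailed coding may sit there or in the full protocol.

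The first three objections stand and limit the claim. The fourth stands in part: a missing instrument or specialty would be no finding alone. But the article does state the outcome, the report to the physician and the two follow-up questions, and together these yield a datum that cannot separate confirmation from acceptance. If the full form already records the assessment, the sponsor can say so in one line.

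It is also fair to object that patients may not know which tests were done. That limits the remedy, and the fix allows for it.

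**Conclusion.** The point holds in a limited form. Confirmation is unblinded and patient-reported, and as worded it does not distinguish a new assessment from agreement with the screen. The confirmed share is therefore not an unbiased measure of how often a positive screen is right.

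Knowledge of the result pushes the share up relative to independent assessment, by 10 to 25.5 points in the assumed scenarios. Against the true share with CI, the range is −23.5 to +26.5 points before any loss to follow-up, so net size and direction are unknown. These figures rest wholly on assumed accuracies and show only that the error could be material either way. The planned CAIDE and ACB comparisons are defined by the s-MoCA group and do not depend on confirmation. This is a worthwhile, cheap improvement and does not undermine the study as a whole.

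**What to change.** Leave referral and the report to the physician unchanged. At the electronic follow-up contact in Section 2.10, add two items:

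1. who assessed the patient (general practitioner or specialist);
2. whether any cognitive assessment other than the pharmacy s-MoCA was done, taken from a medical report where the patient has one.

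Report four categories separately: confirmed after further assessment, accepted without further testing, not confirmed, and not seen or no response. State that the share is unblinded and not an accuracy estimate; the new items do not remove the physician's knowledge of the screen. The follow-up contact is the safer place for these items, because the article describes Supplementary Table 3 only as information going out to the physician and shows no return section.

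The cost is two items at a contact already planned. The downsides are a lower headline confirmed share (in the illustration with s = 0.30, 28% in place of 58%, with the other 30% shown as accepted only) and some patient-recall error in the new items.

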### Cognitive screening

2.6

The gold standard screening tool, the Montreal Cognitive Assessment (MoCA), one of the available cognitive screening instruments, scans seven cognitive domains: executive functioning; visuospatial abilities; language; attention, concentration and working memory; abstract reasoning; memory and orientation, will be used. We use the short variant (s-MoCA) (28, 29) in the Slovak language, presenting a comparable alternative for detecting MCI and dementia. This short variant consists of 8 items. These items measure visuospatial and executive functions (trail making and clock drawing), language abilities (animal naming – rhinoceros), attention (serial 7 s – counting by subtracting seven), verbal fluency (naming for 1 min), abstraction (watch), delayed recall of words, orientation (place) (29). According to our previous outcomes, this simple, shortened version is an easy-to-use cognitive screening. It is an applicable compound of pharmaceutical care for adult patients aged 50 and older with cardiovascular disease and/or suspected metabolic syndrome (sMetS) to explore their cognitive state. This shortened form of the MoCA scale has a range of 0–16 points; the time of completion is 5–7 min (which is only one-third the length of the original MoCA), and a cut-off of ≤12 represents a cognitive impairment (29).

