## Statistical analyses and mitigation of bias

4

The obtained data will be analyzed using GraphPad, version 8.0.1 (GraphPad Prism, San Diego, CA, USA) and the SAS Education Analytical Suite for Microsoft Windows, version 9.3 (SAS Institute Inc., Cary, NC, USA). We will perform fundamental descriptive analyses (calculation of mean and SD), normality tests for the included variables, correlation tests, *t*-tests for two independent variables, and one-way analysis of variance (ANOVA) in the case of more independent groups. Multivariate regression models will be used to compare cognitive outcomes across subgroups.

Since there is no randomization or intervention control in this study, several types of bias can affect validity. In the study, we will mitigate selection bias through design-stage (broad and inclusive recruitment, clear criteria, consistent enrolment) and analysis-stage strategies (statistical adjustment, sensitivity analyses). Observer bias will be mitigated through standardization, pharmacist training, objective measurements, and data monitoring strategies. Social desirability bias will be mitigated through use of questionnaire design (e.g., using neutral wording and validated scales) and through pharmacist training with a focus on his/her empathy and neutrality.

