#### Study objectives

5.1.1

To perform a standardized cognitive screening by a trained pharmacist within advanced pharmaceutical care in a community pharmacy.To test the association between the presence of modifiable Cardiovascular Risk Factors, Aging, and Incidence of Dementia (according to The CAIDE Dementia Risk Score) and poorer cognitive abilities (expressed s-MoCA score) in the adult population aged 50+.To assess the medication use related to CI by medication analysis as a part of pharmaceutical counseling in a community pharmacy.

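### Section 3 relates CAIDE and ACB to cognition only through a split of the s-MoCA at 12, Objective 2 is worded on the score, and no main association analysis is named

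*Protocol article*

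**What the plan says.** Section 2.6 describes the instrument: "This shortened form of the MoCA scale has a range of 0–16 points", and "a cut-off of ≤12 represents a cognitive impairment".

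Section 3 (Outcomes) builds the study group on that threshold, namely adults with "lower cognitive abilities expressed by s-MoCA scores (≤ 12 points". These participants are CI+. Their CAIDE results and "the use of risk medications (expressed by ACB score) and then compare them with a control group" make up the comparison. Who belongs to the control group is not stated.

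Objective 2 in Section 5.1.1 concerns the association of CAIDE with "poorer cognitive abilities (expressed s-MoCA score) in the adult population aged 50" and over. Objective 3 says only that medication use related to impairment will be assessed.

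Section 4 gives a general list of methods that includes "normality tests for the included variables, correlation tests", *t*-tests, ANOVA and multivariate regression of cognitive outcomes across subgroups. It does not say which variables enter the correlations or on what scale the regression outcome is taken. Section 2.7 compares s-MoCA performance between participants with and without suspected metabolic syndrome, which is a separate question.

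**The concern.** Section 3 is the only place that fixes how CAIDE and ACB are to be related to cognition, and it does so by dividing participants at 12. In that comparison a score of 0 counts the same as a score of 12, while 12 and 13 fall on opposite sides. Objective 2 is expressed on the score. The two are different analyses of the same question, and the article does not rank them.

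Two things are at stake. First, a split outcome gives a less precise estimate from the same participants. Second, the result depends on a control group that could be everyone above 12, a matched subset or something else. The sample size in Section 2.2 was set for the precision of a proportion, so no reserve was planned for these associations.

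**Working it through.** **The plan's own figure.** Section 2.2 gives a minimum of 385 for a 95% confidence interval, a 5% margin of error and a population of 2,033,555. With an assumed proportion of 0.5 (not stated):

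n = 1.96² × 0.25 / 0.05² = 384.15, rounded up to 385. With the finite-population correction it is 384.07, again 385. The figure reproduces. It concerns a proportion, not an association.

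**Inputs for the split.** From the documents: range 0–16, cut-off ≤12, n = 385. Not in the documents, hence assumed: the CI+ share p (10% to 50%), an illustrative correlation of 0.15 between a risk score and s-MoCA, a linear association, and a two-sided 5% test.

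**Formula.** For a normally distributed score split so that a share p lies below the cut, the information kept relative to the full score is

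E = φ(z_p)² / [p(1 − p)].

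At p = 0.25: φ(z_p) = 0.318, so E = 0.318² / 0.1875 = 0.539. The loss is 46%, and 385 participants carry the information of 385 × 0.539 ≈ 207.

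**Power**, by Fisher's z with n = 385: Φ(atanh(r) × √382 − 1.96). The full score with r = 0.15 gives 0.840. For the split, r is replaced by r√E; at p = 0.25 this is 0.15 × √0.539 = 0.110, which gives 0.579.

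| Assumed CI+ share | E | Loss | Equivalent n | Power, split (full score 0.840) |
|---|---|---|---|---|
| 10% | 0.342 | 66% | 132 | 0.405 |
| 15% | 0.426 | 57% | 164 | 0.484 |
| 20% | 0.490 | 51% | 189 | 0.540 |
| 25% | 0.539 | 46% | 207 | 0.579 |
| 30% | 0.576 | 42% | 222 | 0.608 |
| 35% | 0.603 | 40% | 232 | 0.628 |
| 50% | 0.637 | 36% | 245 | 0.652 |

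**Check without the normal assumption.** The s-MoCA is an integer with a ceiling, so the comparison was repeated by simulation with a score rounded and truncated to 0–16 and split at ≤12. The means and SDs are assumed.

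| Mean, SD | CI+ share | Loss against the 0–16 score |
|---|---|---|
| 12.5, 3 | 50% | 33% |
| 13, 2.5 | 42% | 34% |
| 13.5, 2 | 31% | 39% |
| 14, 2 | 23% | 43% |
| 14.5, 2 | 16% | 50% |

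The losses are somewhat smaller than under normality (50% against 56% at a 16% share), but none is below about a third.

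**The case against.** The strongest reply is that the split is not the only analysis. Section 4 provides for correlation tests and regression, and Objective 2 speaks of the score. Matching each pair of variables to a test is commonly left to a fuller document. This stands in part: an analysis on the score is not excluded. But Section 4 names no variables, and its regression is itself described as a comparison across subgroups. A general list does not settle which analysis answers Objective 2 when Section 3 specifies a different one.

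Second, the cut-off is taken from the cited source for the instrument, and it serves the study's purpose of identifying people for medical assessment. This stands. Describing risk factors among screen-positives is a legitimate question, which is why the split should be kept as a secondary comparison.

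Third, an association of ACB with cognition is not listed as an objective. That is correct for Section 5.1.1, but Section 3 plans to compare ACB between the groups, so the association is already being examined.

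Fourth, the size of the loss depends on quantities that the documents do not give. This stands fully and limits what can be claimed.

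**Conclusion.** The point holds in a limited form. Section 3 specifies a split comparison against an undefined group, Objective 2 is worded on the score, and the main association analysis is not identified. If the split is used, the loss of information is about a third or more. Under a normal score it is 36% to 66% for CI+ shares from 50% down to 10%, and somewhat less for a discrete score with a ceiling. This rests on an assumed CI+ share and a linear association.

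Three stronger readings are tempting, and the documents support none of them:

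- A reader might infer that the plan discards the score altogether. Section 4 leaves an analysis on the score open.
- A reader might attach one fixed percentage. A band of 40–55%, for instance, needs a CI+ share of about 17–34% (or, by symmetry, 66–83%) under normality, and no share is stated.
- A reader might conclude that the study is underpowered. No power target or effect size is given for these associations, and 385 is a minimum set for another purpose, so the power figures only illustrate the contrast between the two analyses.

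**What to change.** In Section 3, name as the main association analysis a regression of the s-MoCA total (0–16) on CAIDE and on ACB in all participants, with robust standard errors. Keep CI+ (≤12) against all other participants (>12) as the secondary comparison, which also defines the control group. The use of the cut-off for referral and physician confirmation is unchanged.

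The cost is a change of wording. Sections 2.1, 2.7 and 2.8 already plan the CAIDE and ACB assessments without limiting them to CI+, so no new data are needed. The downside is that the main results are expressed in s-MoCA points, which are less directly tied to screening status; the retained secondary comparison covers that.

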## Statistical analyses and mitigation of bias

4

The obtained data will be analyzed using GraphPad, version 8.0.1 (GraphPad Prism, San Diego, CA, USA) and the SAS Education Analytical Suite for Microsoft Windows, version 9.3 (SAS Institute Inc., Cary, NC, USA). We will perform fundamental descriptive analyses (calculation of mean and SD), normality tests for the included variables, correlation tests, *t*-tests for two independent variables, and one-way analysis of variance (ANOVA) in the case of more independent groups. Multivariate regression models will be used to compare cognitive outcomes across subgroups.

Since there is no randomization or intervention control in this study, several types of bias can affect validity. In the study, we will mitigate selection bias through design-stage (broad and inclusive recruitment, clear criteria, consistent enrolment) and analysis-stage strategies (statistical adjustment, sensitivity analyses). Observer bias will be mitigated through standardization, pharmacist training, objective measurements, and data monitoring strategies. Social desirability bias will be mitigated through use of questionnaire design (e.g., using neutral wording and validated scales) and through pharmacist training with a focus on his/her empathy and neutrality.

## Discussion

5

### Objectives and hypotheses

5.1

#### Study objectives

5.1.1

To perform a standardized cognitive screening by a trained pharmacist within advanced pharmaceutical care in a community pharmacy.To test the association between the presence of modifiable Cardiovascular Risk Factors, Aging, and Incidence of Dementia (according to The CAIDE Dementia Risk Score) and poorer cognitive abilities (expressed s-MoCA score) in the adult population aged 50+.To assess the medication use related to CI by medication analysis as a part of pharmaceutical counseling in a community pharmacy.

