### Design and setting

2.1

We designed a study protocol for a prospective observational clinical cohort study in Slovakia to evaluate multifactorial and specific risk factors for CI in the adult population aged 50+ as a part of advanced pharmaceutical care in community pharmacies (Figure 2). The current study protocol is developed based on our previous findings (39, 40) and offers an advanced method of identifying patients at risk for CI by pharmacist intervention. Firstly, we focus on performing a cognitive screening using a short version of the Montreal Cognitive Assessment (21, 28). Secondly, we will assess the risk of developing dementia according to the CAIDE Dementia Risk Score, which includes lifestyle factors, age, and comorbidities altogether expressed as the CAIDE score (31). Third, we will assess the risk of medication use by impacting cognitive health according to the ACB scale using the free available online ACB calculator (41).

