### Assessment of dementia risk factors

2.7

The CAIDE scoring system will be applied to the occurrence of modifiable risk factors (31). It was designed to determine the risk of developing dementia in cognitively intact individuals aged 40 to 65 years. This tool assesses common, easy-to-obtain, measurable data such as age, sex, education, blood pressure, cholesterol level, BMI, and physical activity. Each item is scored, and the resulting score represents the level of risk of developing cognitive impairment or dementia. The cut-off score represents 8–9 points for low and normal risk. Higher scores (10–15) indicate an increased risk of developing cognitive impairment (31).

We will also assess an occurrence of the suspected MetS (sMetS) as it can be easily identified in community pharmacy and may affect cognitive function (40, 44). The presence of sMetS will be estimated according to the International Diabetes Federation Worldwide Definition of MetS (45), 2005, modified for the European population (46). Accordingly, patients will be divided into groups according to the presence or absence of sMetS (sMetS+; sMetS-), and we will compare cognitive abilities in the test s-MoCA between two subpopulations (sMetS+/sMetS-) (40).

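### Objective 2 uses the total CAIDE score to measure modifiable risk factors, but the total also contains age, sex and education, so its association with s-MoCA cannot by itself support a conclusion about modifiable factors

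*Protocol article*

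**What the plan says.** Objective 2 (section 5.1.1) sets the exposure as "the association between the presence of modifiable Cardiovascular Risk Factors, Aging, and Incidence of Dementia (according to The CAIDE Dementia Risk Score") and the outcome as "poorer cognitive abilities (expressed s-MoCA score) in the adult population aged 50" and over.

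Section 2.7 gives CAIDE the same purpose: "The CAIDE scoring system will be applied to the occurrence of modifiable risk factors". The same paragraph says that the tool assesses "measurable data such as age, sex, education, blood pressure, cholesterol level, BMI, and physical activity", and that "Each item is scored, and the resulting score represents the level of risk of developing cognitive impairment or dementia". Section 2.1 describes the score as one "which includes lifestyle factors, age, and comorbidities altogether expressed as the CAIDE score".

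The Outcomes section states the comparison: in the CI+ group "we will collect data on the prevalence of CI risk factors (expressed by CAIDE score"), to be set against a control group.

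Section 4 lists correlation tests, t-"tests for two independent variables, and one-way analysis of variance (ANOVA) in the case of more independent groups". It adds regression models for comparing cognition between subgroups, and mentions statistical adjustment in general terms as a remedy for selection bias. The article defines no modifiable-only part of CAIDE and does not name age, sex or education as covariates.

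**The concern.** Age and sex cannot be modified, and years of schooling are essentially fixed by age 50. The article's own introduction describes cognitive decline with age, and its s-MoCA cut-off of 12 or below carries no stated correction for age or education. CI+ patients can therefore be expected to be older, and age adds points to CAIDE. A CAIDE difference between CI+ patients and controls, or a correlation of CAIDE with s-MoCA, could then appear even if blood pressure, cholesterol, BMI and activity contributed nothing.

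What is at stake is how objective 2 is read. Section 1.2 argues that pharmacists can influence most of these factors. A significant total-score result labelled as modifiable would seem to support that argument without having tested it.

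**Working it through.** **Stated figure.** The only number in the plan that bears on this is the sample size (section 2.2): 95% confidence, 5% margin, N = 2,033,555. With an assumed proportion of 0.5, n = 1.96² × 0.25 / 0.05² = 384.15. With the finite population correction it is 384.07. Both round up to the stated 385. This is a precision calculation for one proportion and does not depend on the objective 2 test.

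**Model.** Write the CAIDE total as T = A + M, where A is the sum of the age, sex and education points and M the sum of the modifiable points. Suppose s-MoCA depends on A only and that A and M are independent. Let f be the share of the variance of T due to A, and r the size of the correlation of A with s-MoCA. Then the correlation of T with s-MoCA is ρ = r × √f in size.

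**Inputs.** n = 385 is from the article. Two-sided alpha 0.05 is assumed, as the article states none. f = 0.30-0.60 and r = 0.2-0.4 are assumed, as the article gives neither item weights nor correlations.

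**Chance that an unadjusted test of T is significant.** By Fisher's z this is approximately Φ(atanh(ρ) × √382 − 1.96).

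| f | r | ρ = r√f | P(p < 0.05) |
|---|---|---|---|
| 0.30 | 0.2 | 0.110 | 0.575 |
| 0.30 | 0.3 | 0.164 | 0.90 |
| 0.40 | 0.3 | 0.190 | 0.964 |
| 0.60 | 0.4 | 0.310 | > 0.999 |

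Widening f to 0.20-0.65 with the same range of r gives 42% (f = 0.20, r = 0.2) to about 100%.

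**What adjustment does.** Substitute T = A + M into a regression on T and A:

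b·T + c·A = b·M + (b + c)·A.

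The coefficient on T is therefore the coefficient on M in a model containing M and A. Adjusting the total for its own age, sex and education points is the same analysis as testing the modifiable part with those points as covariates.

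**Simulation check** (2,000 replicates per setting, n = 385, no modifiable effect):

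| f | r | T alone | M adjusted for A | T adjusted for A |
|---|---|---|---|---|
| 0.20 | 0.2 | 0.430 | 0.059 | 0.059 |
| 0.20 | 0.3 | 0.748 | 0.054 | 0.054 |
| 0.35 | 0.3 | 0.939 | 0.046 | 0.046 |
| 0.50 | 0.3 | 0.988 | 0.055 | 0.055 |
| 0.50 | 0.4 | 1.000 | 0.052 | 0.052 |

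The two adjusted analyses agree exactly and reject in about 5% of runs.

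**The case against.** The strongest case on the other side has three parts.

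1. **Objective 2 can be read as overall CAIDE risk.** Its wording largely spells out the CAIDE name, which includes aging, and the abstract even lists aging among modifiable factors. On that reading the total-score test is the right test. This stands as far as it goes, and it is why rewording is an acceptable fix. It does not remove the mismatch, because section 2.7 separately assigns CAIDE to modifiable factors while listing items that are not modifiable.

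2. **Section 4 already plans regression and adjustment, and a condensed article may leave the covariate list to a fuller document.** An unnamed covariate list would indeed be no finding. But section 4 offers adjustment for selection bias and regression for subgroup comparisons, beside unadjusted correlations and t-tests. The Outcomes section compares the total as such, and nothing in the article separates modifiable from other items. The point concerns what the article says CAIDE measures.

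3. **The percentages are built on assumptions.** This is correct. The article supplies neither f nor r, and independence of A and M is a simplification.

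A reader might also infer that regression cannot help, because adjusting the total for age and education adjusts the exposure for part of itself. The identity above shows the opposite: with those components entered as scored, adjustment solves the problem.

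**Conclusion.** The point holds as one of construct and interpretation. The total CAIDE score answers whether overall CAIDE risk goes with lower s-MoCA. It cannot by itself answer whether modifiable factors do. For that conclusion it is enough that age, sex or education relates to s-MoCA. The size, about 57% to over 99% of studies significant with no modifiable effect, is an illustration for an unadjusted test under the stated assumptions.

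Three stronger readings are not supported:

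- The 57% to over 99% might be taken as an inflated type I error. It is not one. In that scenario the total really is associated with s-MoCA, so rejecting the total-score null is correct. The 5% comparator belongs to a different hypothesis, about the modifiable part.
- The third hypothesis might seem to fall with objective 2. It says only that pharmacists could help monitor modifiable factors, which no CAIDE association would establish or refute.
- The same fault might be assumed in the metabolic syndrome and anticholinergic burden comparisons. Nothing worked through here shows that.

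Risk factors are a secondary aim and the sample size is unaffected, but the correction is nearly free.

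**What to change.** For objective 2, regress s-MoCA (0-16) on the modifiable CAIDE part (blood pressure, cholesterol, BMI and physical activity, as scored for CAIDE), with age, sex and years of education as covariates. Using the CAIDE total adjusted for its own age, sex and education points is equivalent; the equality is exact when the same points are entered. Report the unadjusted CAIDE comparison between CI+ and controls as overall risk only. If the sponsor prefers to keep the total score as the analysis, drop the word modifiable from objective 2 and from any conclusion drawn from it, and align section 2.7.

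**Cost.** A paragraph of wording, slightly more analysis work, and possibly a weaker association to report. No extra participants are needed, and 385 does not change. Age, gender and school years are already in Table 2.

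**One thing to reconcile.** Table 2 is presented as the summary of all recorded items. It has hypertension and dyslipidaemia as Yes/No and waist circumference, but no BMI, blood pressure value or cholesterol level, whereas section 2.7 lists those among the CAIDE items. The planned total needs these inputs anyway, so the fix adds no data burden, but the two sections should agree.
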